**Sample Size and Power Calculation**

If we assume a 40% abstinence rate at end of treatment in the varencline plus sham tDCS group, the abstinence rate in the active tDCS group would need to be double that or 80% in order to see a statistically significant difference with n=25 per arm, p <0.05, and 80% power. As such we do not expect to see a statistically significant difference between the two treatment arms at 25 subjects per arm.

For the treatment part of the study, the main purpose of the study is to establish an Effect Size for tDCS as an adjunct to standard varenicline treatment. This is independent of the number of subjects but allows us to estimate the N that would be required to achieve statistical significance depending on the effect size we observe. The effect size measure we will use will be the partial η2 generated by SPSS and is described in greater detail below.

For the MRI portion of the study, 15 to 25 subjects per group is standard in the neuroimaging field and is more than sufficient to detect significant within- and between-group differences in brain activity.

**Data Analysis**

Continuous data (cravings, mood, cigarettes smoked/day, CO) will be assessed with 2 Gender x 2 (Laterality) x 10 (session) Analyses of Variance (ANOVA). Parallel ANOVAs will assess self-report measures during post-treatment follow-up. Categorical data (e.g., # abstinent participants/session) will be assessed with chi-square, and Kaplan-Meyer survival analysis for repeated measures. Planned comparisons will be performed for the critical experimental conditions (active tDCS) vs. sham.

The critical metric will be Effect Size (partial η2 generated by SPSS), rather than p level. This will reveal the degree of efficacy for the primary outcome variable, Consecutive Days Abstinent (small = .01, medium = .06, large = .14), and allow us to estimate N required to achieve statistical significance for this effect (80% power, α = .05, two-tailed). Pearson correlations will explore the possible relationship between effects of tDCS (session 10 scores, controlling for session 1) and trait factors (e.g., FTND, age, gender, depression).Analysis of MRI data

For the neuroimaging data, brain imaging measures will be compared between groups and across time points, using analysis of variance. MRI measures will also be related to subjective responses (i.e., baseline scores and changes in craving, mood, and withdrawal) using linear regression.

fMRI data will be analyzed by fitting a general linear model (GLM) to the data time-series at every voxel across the brain (and/or within ROIs) and assessing effects using F/t-tests and % signal change calculations. Quantitative T1 maps and DTI analysis will be analyzed at the whole brain level and using ROIs.

After back-sorting by treatment outcome (achieved/maintained abstinence), we expect baseline measures to predict relapse, and active tDCS treatment to result in more efficient functional activation, . than sham tDCS at the second MRI scan.

Analysis of Eye-Tracking Data

For the eye-tracking data, gaze position data are processed by VAST into sequences of fixations and saccades and summary statistics of visual scanning parameters are computed. The VAST parameters include: the number of fixations, the average fixation duration, the average saccadic amplitude and the number of transitions for each image type. These parameters are sensitive measures of attentional bias for different visual cues. The outcome measures of this paradigm will be analyzed using a mixed-model analysis of variance (ANOVA). The within-groups factors are the image types (smoking, neutral, high valence) and session (sessions 1, 2, 3,4 and 5) and the between-groups factor is group (active tDCS and sham tDCS). Pearson’s product–moment correlations will be conducted between parameters of attentional bias and subjective craving scores. Through analysis, we will investigate and compare the treatment effects of varenicline and active tDCS on attentional bias in different sessions. We will also examine the relationship between changes in attentional bias and craving.

By means of a mixed design repeated-measures ANOVA, the VAST parameters will be compared within-subjects at 5 sessions to investigate the effects of varenicline treatment. The parameters will also be compared between the two groups of subjects to examine the treatment effects of active tDCS. We will also compare the VSB parameters of those who quit smoking in the last 4 weeks of treatment and those who were unable to remain abstinent to find out the possible indicators of treatment outcome. Pearson correlation method will be used to explore the relationships between: a) subjective craving and VSB parameters, b) sensation seeking behavior as measured by the sensation seeking scale measures and VSB parameters. Also we will use recurrent neural networks (Chung et al, 2018) to analyze differences between fixation sequences of patients that were treated with tDCS and patients that were not, and between patients that quit smoking and those that were not. Using Cox regression of survival analysis, we will also investigate the correlation between the length of abstinence (time to relapse) and VSB parameters associated with smoking cues, negative emotional cues and high-arousal/high-risk cues.

All data analysis will be conducted using SPSS, SPM or R as appropriate.

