**Procedures**

Following the initial assessment appointment to obtain consent and confirm eligibility, the first tDCS treatment session will be booked. A breathalyser will screen for alcohol and expired CO at each tDCS session. The tDCS stimulation will take place in a quiet room, free of distractions. Stimulation will continue uninterrupted for 20 minutes with the experimenter in the room. While being stimulated, subjects will be required to read self-help materials related to smoking cessation, relapse prevention, and mood management. The readings for each day of stimulation will be standardized for all subjects.

To increase the opportunity to detect an acute beneficial effect of tDCS, participants will be asked to refrain from smoking for 2 hours prior to the start of each treatment session. Relative CO readings from the first day (ad lib smoking) compared to subsequent days will provide a coarse means of verifying compliance with the 2-hour pre-session smoke-free requirement.

Participants will be randomly assigned (1:1) to one of 2 treatment arms (double-blind). Participants will be matched as closely as possible on age, gender and cigarettes per day.

There will be 10 consecutive daily sessions of tDCS with the anode over the left DLPFC and cathode over the right DLPFC (active or sham) (Monday-Friday for 2 weeks; 2 mA x 20 min). Participants assigned to sham will have electrodes placed identically to active but receive only 30 seconds active stimulation. Participants will also be videotaped during each tDCS session to ensure consistency of tDCS application between research personnel and for documenting participant reactions during the session. This will also be used to document any side effects/complications participants may experience during the session. Each video tape session, as well as all data collected in the trial, will be stored on a secure server and will be retained for 10 years after the participant completes the study, as suggested by CAMH’s policy on Storage of Records. After each tDCS session, the video footage will be transferred from the camera to the secure server.

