**Outcome Measures**

The primary outcome measure will be continuous abstinence from smoking during weeks 9 – 12 as reported at clinic visits during those 4 weeks and confirmed using expired CO. Subjects will be classified as treatment responders if they respond “no” to the question: Have you smoked any cigarettes (even a puff) in the last seven days?

The key secondary outcome measures are:

1. Self-reported 7 day point prevalence abstinence throughout weeks 2 to 12 confirmed by expired CO at each clinic visit. To calculate survival curves we will also collect self-reported continuous abstinence weeks 9 through 26. For weeks 13 to 25, this will be collected via email or text message. For week 26, subjects will attend a brief clinic visit so abstinence can be confirmed with expired CO and urinary cotinine using a semi-quantitative dipstick. We hypothesize that the active tDCS group will have higher rates of abstinence (less relapse) than the sham tDCS group.

2. fMRI: change in Blood Oxygen Level Dependent (BOLD) activation in brain regions known to be associated with drug craving and emotion processing/regulation. MRS: GSH levels measured in a single voxel placed over prefrontal cortex. Fractional anisotropy (FA) values will be extracted from DTI analysis from regions of interest (ROIs) or to form probabilistic tractography for the whole brain. Network maps will be extracted and analyzed from the resting state functional connectivity measure.

3. Eye Tracking tests: changes in attentional bias to smoking-related cues and negative emotional cues. Attentional bias to high-arousal/high-risk cues.

*Self-Report Measures*

Participants will complete the 10-item Questionnaire of Smoking Urges-Brief (QSU-10; Tiffany and Drobes, 1991) and the Minnesota Nicotine Withdrawal Scale (MNSW; Toll et al, 2007) at each treatment session upon arrival and immediately after tDCS. They will complete a Side Effects Checklist ([name] et al., 1995) at the end of each treatment session.

Trait scales to be completed at baseline will include the FTND (Heatherton et al 1991) and Alcohol Use Disorders Identification Test (Saunders et al., 1993), 90-day Alcohol Timeline Followback (TLFB; Sobell and Sobell, 1992); 30-day Tobacco Timeline Followback (adapted from alcohol TLFB); Sensation Seeking Scale (Zuckerman et al., 1978).

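### Craving and withdrawal are scored before and after each tDCS session, but no analysis stated in the protocol isolates the acute active-minus-sham change

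*Protocol*

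**What the plan says.** Three places in the protocol bear on this.

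- **Outcome Measures, Self-Report Measures.** The QSU-10 and the Minnesota withdrawal scale are completed "at each treatment session upon arrival and immediately after tDCS". Every treatment session therefore gives a matched pair of scores per participant.
- **Procedures.** The smoke-free period before each session has a stated purpose: "To increase the opportunity to detect an acute beneficial effect of tDCS, participants will be asked to refrain from smoking for 2 hours". The same section gives the number of daily sessions: "There will be 10 consecutive daily sessions of tDCS".
- **Data Analysis.** The model for these scores is written out factor by factor: "Continuous data (cravings, mood, cigarettes smoked/day, CO) will be assessed with 2 Gender x 2 (Laterality) x 10 (session) Analyses of Variance (ANOVA". It is followed by "Planned comparisons will be performed for the critical experimental conditions (active tDCS) vs. sham", with no time point and no dependent variable named. The only score that the section defines as an effect of stimulation is "effects of tDCS (session 10 scores, controlling for session 1", which is a contrast between sessions.

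**The concern.** An acute effect of stimulation is the difference between arms in how a score moves from just before to just after a session. The protocol collects both readings and asks participants to abstain before each session so that such an effect can be seen. The model it then writes down has one cell per session. It has no before/after factor, does not define the dependent variable as a change, and does not say which of the two readings enters.

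The other analyses that use craving do not fill the gap. The session 10 score controlling for session 1 is between sessions. The MRI regression relates imaging measures to baseline scores and to unspecified changes in craving. The eye-tracking correlations relate craving to gaze parameters. By contrast, the eye-tracking ANOVA does name its within-subject factors (image type and session) and its group factor.

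An analyst who follows the text must therefore choose a reading, and the possible choices estimate different quantities. The protocol makes effect size its critical metric, so the choice decides what the reported effect size for craving refers to.

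**Working it through.** **The plan's own figure.** The protocol gives no number on this point. Its one sample-size statement (40% against 80% abstinence, 25 per arm, 80% power) reproduces: the uncorrected normal approximation gives 23 per arm, and a two-sided Fisher exact test with 25 per arm has power 0.788. Nothing below depends on it.

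**Step 1: readings against cells.** Ten daily sessions with two readings each give 10 × 2 = 20 scores per scale per participant. The stated ANOVA has 10 session cells.

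**Step 2: what each choice estimates.** Let D be the arm difference (active minus sham) at arrival in a given session, and d the arm difference in acute change.

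- Arrival score: D. It carries none of that session's acute effect.
- Post-session score: D + d.
- Average of the two: (D + D + d)/2 = D + d/2.
- Change, post minus arrival: (D + d) − D = d.

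At session 1, D is chance imbalance. From session 2 it can also contain lasting effects of earlier sessions. Only the change isolates d. This step needs no assumed figure.

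**Step 3: size.** From the protocol: 25 per arm, 10 daily sessions, two-sided 0.05. Assumed, because the protocol gives no variances: person a = 0.5, session within person b = 0.1, residual e = 0.4. These sum to 1, so effects are in SDs of one arrival score, and the before/after correlation within a session is (0.5 + 0.1)/1 = 0.6. Person-level variation in acute response is h = 0.1 (range 0 to 0.3).

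Variance V of a participant's 10-session mean:

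- Average: a + h/4 + (b + e/2)/10 = 0.5 + 0.025 + 0.03 = 0.555
- Post only: a + h + (b + e)/10 = 0.5 + 0.1 + 0.05 = 0.65
- Change: h + 2e/10 = 0.1 + 0.08 = 0.18

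The standard error of the arm difference is √(2V/25). Power is from the noncentral t with 48 degrees of freedom.

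| Score analysed | Effect at d = 0.3 | SE | Effect/SE | Power (h = 0 to 0.3) | Power at d = 0.5 |
|---|---|---|---|---|---|
| Average | 0.15 | 0.211 | 0.71 | 11% (11% to 10%) | 21% |
| Post only | 0.30 | 0.228 | 1.32 | 25% (29% to 20%) | 58% |
| Change | 0.30 | 0.120 | 2.50 | 69% (96% to 39%) | 98% |

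Change has the smaller variance than post-only whenever 2e/10 < a + (b + e)/10, that is, e < 10a + b. With a much lower correlation of 0.2 (a = 0.1, b = 0.1, e = 0.8) this still holds (0.8 < 1.1), but the lead shrinks: 53% for change, 49% for post only and 24% for the average at d = 0.3, h = 0.1.

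**Step 4: the same point in the protocol's metric.** For two equal groups η² = δ²/(δ² + 4), where δ² = effect²/V. At d = 0.3:

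- Average: δ² = 0.0225/0.555 = 0.041, η² = 0.010
- Post only: δ² = 0.09/0.65 = 0.138, η² = 0.033
- Change: δ² = 0.09/0.18 = 0.50, η² = 0.111

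The protocol's benchmarks are 0.01, 0.06 and 0.14. One and the same acute effect would be described quite differently depending on the reading used.

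**Step 5: why not adjust for the arrival score.** A model with the post-session score as outcome, the same-session arrival score as covariate and a random intercept per participant looks natural, so it was simulated with these variances. The fitted arrival slope is only about 0.3. Suppose there is no acute effect but a lasting 0.5 SD reduction from session 2 on. The mean shift over ten sessions is 0.5 × 9/10 = 0.45, in arrival and post scores alike. The covariate removes 0.3 × 0.45 = 0.135 and leaves 0.45 − 0.135 = 0.315 as a false acute effect. The simulated bias was about −0.31 to −0.32 SD, and the test rejected in between about one third and two thirds of runs, while the change score stayed near 5%. With a true acute effect of 0.3 SD and h = 0.1, the covariate model had roughly 30% to 40% power against about 70% for change.

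**The case against.** The strongest reply is that the protocol says only that cravings will be analysed and does not define the score. A within-session change would fit the ten-session layout unchanged. Together with the planned active-versus-sham comparisons, it would then estimate exactly the acute effect. This stands. A reader might infer from the missing factor that the acute effect can never be estimated, or that the trial will leave it untested. The protocol does not support that: a change score is compatible with the layout, and an analysis plan not shown may specify one. What can be said is that the protocol writes out its factors and names neither a change score nor a before/after term.

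A reader might also infer that an acute craving effect is one of the trial's aims. It appears in none of the objectives, research questions or hypotheses, and it is not a primary or key secondary outcome. The clause in Procedures speaks of an acute benefit without naming craving. This stands too and lowers the priority.

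Power is a secondary yardstick here, because the protocol puts effect size ahead of p values and every variance above is assumed. The large gap to the average also matters only if someone averages, which the protocol does not propose. The fair practical comparison is change against post-only, where the gain runs from large to small as the before/after correlation falls. The algebra in step 2 does not depend on any of this.

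Finally, the same sentence has a larger defect. It names no treatment arm, and its laterality factor has a single level, because all participants have electrodes placed "with the anode over the left DLPFC and cathode over the right DLPFC (active or sham". A before/after term alone would therefore not give a tDCS effect, so the remedy must include arm.

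**Conclusion.** The point holds in this form: paired scores are collected at every session, the smoke-free period is justified by an acute effect, and no analysis stated in the protocol isolates the active-minus-sham difference in within-session change. Of the single readings that could enter the ANOVA, arrival scores carry none of that difference, the average carries half, and post-session scores confound it with differences present at arrival.

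Under the assumed variances, a 0.3 SD acute effect has about 69% power with change (96% to 39% as person-level variation in response goes from 0 to 0.3), against 25% with post scores and 11% with the average. These figures rest wholly on assumed variance components. The ordering held at every setting tried, but the lead over post scores is small when the two readings are weakly correlated. Because the outcome is ancillary, this is a worthwhile correction of modest priority and does not threaten the trial's main conclusions.

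**What to change.** In the Data Analysis section:

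- **Acute effect.** For the QSU-10 and the withdrawal scale, analyse the within-session change (post minus arrival) with arm, session and arm-by-session as fixed effects and participant as a random effect. The acute effect is the active-minus-sham difference in change. Equivalently, keep both readings and add a before/after factor. The estimate is then the arm-by-before/after interaction, and the random terms must cover participant, participant-by-session and participant-by-before/after.
- **Cumulative effect.** Analyse arrival scores in a separate model by arm and session, so that lasting and acute effects are reported apart.
- **Avoid.** Do not enter the same-session arrival score as a covariate in a random-intercept model. From session 2 on it is measured after randomisation and can carry earlier tDCS effects, which would then appear as a false acute effect.

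The cost is a few lines of text and one extra model per scale. All the data are already collected. The rewrite can be made together with naming treatment arm in the same sentence.

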**METHODS**

**Design**

This will be a double-blind sham-controlled two-arm randomized clinical trial. Fifty participants will be randomized (1:1) to each arm. Arm 1 will be active tDCS plus varenicline (n=25) and Arm 2 will be sham tDCS plus varenicline (n=25). Treatment duration will be 12 weeks. Subjects will be required to attend an in person assessment visit. They will then be randomized to a condition. Neuroimaging scans (fMRI) and eye-tracking tests will be conducted in all participants at baseline. Participants will undergo two scans at baseline on different days within the same week: one in a satiated state and one in a non-satiated state. The same tasks will be performed at each scan. s. Following the baseline fMRI scans and eye-tracking tests, subjects will start taking the varenicline simultaneous with starting the tDCS regimen whereby they will come to the clinic every day (Monday to Friday) for the first 2 weeks to undergo the stimulation (active: 20 minutes at 2mA, sham: 30 seconds at 2mA and then nothing). Their target quit date will be at the end of this 2 week period. They will return to the clinic every two weeks for the next 10 weeks for a booster tDCS session and to complete questionnaires. Eye tracking tests will be conducted at the end of the fourth and eighth weeks. At the end of the 12-week treatment period they will undergo a third fMRI scan and eye-tracking tests. For the next 14 weeks they will be contacted weekly by e-mail or text message to report on their smoking status as measured by the 7 day point prevalence abstinence question. “Have you had a cigarette, even a puff, in the last 7 days?” At the 6-month time point subjects will be asked to return to the clinic for a brief visit to confirm smoking abstinence using expired CO and urinary cotinine and to complete questionnaires.

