**tDCS**

A battery operated tDCS device (SmartStim Model 1000; Nuraleve, Inc., Sudbury ON) with a maximum 4 mA capacity will be used to administer stimulation. tDCS will be applied by two cutaneous anodal and cathodal electrodes – 35cm^2^ and 100cm^2^, respectively. Each electrode will consist of conductive carbon enclosed in a saline-soaked sponge connected to lead wires attached to the tDCS device. An elasticized headband will hold the electrodes in place. The electrode configuration will be left anodal tDCS following the montage successfully demonstrated in a number of tDCS addiction studies (Boggio et al. 2009; Fregni et al. 2008a). The anode and cathode will be applied to the F3 and F4 regions, respectively, as defined by the standard International EEG 10-20 system (Jasper 1958). Stimulation will consist of 2 mA direct current delivered continuously for 20 min. This conforms to parameters of a recent 5-session study on cigarette craving (Boggio et al., 2009) and numerous other studies with clinical (depressed, substance dependent) and healthy participants (see Feil and Zangen, 2011 for review). Active treatment will consist of a current ramp up over 30 seconds to minimize discomfort, followed by 2mA stimulation over 19 minutes and subsequent ramp down over the final 30 seconds. Sham treatment will include a 30 second ramp up and 30 second ramp down at the beginning and end of the treatment session since tingling is commonly felt at the onset and termination.

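### The ANOVA for craving, mood, cigarettes per day and CO has a Laterality factor that the trial does not vary and no treatment-arm factor, so the planned active versus sham comparison cannot be drawn from it

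*Protocol*

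**What the plan says.** The Data Analysis section fixes the factors for four continuous measures: "Continuous data (cravings, mood, cigarettes smoked/day, CO) will be assessed with 2 Gender x 2 (Laterality) x 10 (session) Analyses of Variance (ANOVA"). It adds parallel ANOVAs for self-report measures in post-treatment follow-up. It then promises planned comparisons of active against sham tDCS, without naming a model, a term or an outcome for them.

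The rest of the protocol describes a different structure:

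- **Randomised factor** (Design): "Arm 1 will be active tDCS plus varenicline (n=25) and Arm 2 will be sham tDCS plus varenicline (n=25").
- **Montage** (Procedures): the ten daily sessions are given "with the anode over the left DLPFC and cathode over the right DLPFC (active or sham"), and "Participants assigned to sham will have electrodes placed identically to active but receive only 30 seconds active stimulation".
- **Device settings** (tDCS): "The electrode configuration will be left anodal tDCS following the montage successfully demonstrated in a number of tDCS addiction studies", with the anode at F3 and the cathode at F4.
- **Timing** (Design): after the two weeks of daily sessions, "Their target quit date will be at the end of this 2 week period". Booster sessions follow every two weeks for ten weeks.

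**The concern.** A two-level factor needs two levels in the data. Laterality has one, because nobody receives a right-anodal montage and sham copies the active placement. The factor that does have two levels, active versus sham, is not listed. The model as written therefore spends a factor on something constant and has no term for the question the trial asks.

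The protocol makes partial eta-squared from SPSS its critical metric, in place of the p-value. SPSS reports that statistic term by term, so a model without an arm term gives none for tDCS. The parallel follow-up ANOVAs inherit the gap if they use the same factors. Whoever runs the analysis will have to change the model, and if the protocol is not corrected first, that choice is made after data are in hand.

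The session factor raises a second, smaller issue. Ten levels describe the daily block only, although the same measures are also taken at the booster visits, after the quit date.

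**Working it through.** **Inputs.** Stated factors: gender (2), Laterality (2), session (10), from Data Analysis. Arms: 2, with 25 participants each, from Design. Montage: one, from Procedures and tDCS. Total tDCS sessions: 15, from Participant compensation.

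**1. The plan's session count.** Ten daily sessions, plus one every two weeks for ten weeks: 10 + 10/2 = 10 + 5 = 15. This reproduces the stated 15 and puts the boosters at weeks 4, 6, 8, 10 and 12. The protocol's only other design figure (80% against 40% abstinence, 25 per arm, 80% power) has no bearing on this point. It reproduces reasonably well: 23 per arm by the pooled two-sided formula without continuity correction, and exact Fisher power of 0.788 at 25 per arm.

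**2. Parameters in the stated model.** A full factorial has 2 x 2 x 10 = 40 cell parameters. With Laterality constant, these terms cannot be estimated:

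| Term | Parameters |
|---|---|
| Laterality | 1 |
| Gender x Laterality | 1 |
| Laterality x session | 9 |
| Gender x Laterality x session | 9 |
| Total lost | 20 |

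That leaves 40 - 20 = 20. A rank check on a design matrix for 50 participants and 10 sessions, with both genders in each arm, gave 40 columns and rank 20.

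**3. Is the arm contrast in the model?** Adding an arm column raised the rank from 20 to 21. Arm is therefore not a combination of the stated terms, and no contrast within the model gives active minus sham. Partial eta-squared for a term is SS(term) / [SS(term) + SS(error)]. Without an arm term there is no SS(arm), and any arm difference is left in the error.

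**4. After the correction.** With arm in place of Laterality, the 2 x 2 x 10 design has 40 columns and rank 40. The arm main effect (1 parameter) and arm x session (9 parameters) are both estimable. No sample-size figure changes.

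**5. Which visits the session factor covers.** Its ten levels equal the ten daily sessions, and Data Analysis also uses session 10, controlling for session 1, as the tDCS effect in its correlations. The Pharmacological treatment section puts the target quit date on the last day of that block. Craving and withdrawal are collected at every treatment session (Self-Report Measures), CO at every tDCS session (Procedures), and mood and smoking behaviour at the boosters (Pharmacological treatment). The five booster visits thus yield the same kinds of data but are not assigned to an ANOVA. The parallel ANOVAs are for post-treatment follow-up, whereas Design sets treatment at 12 weeks, so on a plain reading they do not cover the boosters.

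**The case against.** The strongest reply is that the intention is clear. The same section promises planned comparisons of active with sham, the MRI measures are to be compared between groups, and the eye-tracking ANOVA names active and sham as its between-groups factor. On this view Laterality is a mislabelled arm factor, and one changed word cures it. Much of this stands: the intent to compare arms is documented, and the minimum correction is that small. But the protocol does not say that Laterality means arm, so that reading is an inference. Reading it as handedness does not help either, since handedness is not among the listed measures and arm would still be missing.

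It also stands that the four measures, as continuous variables, are neither the primary outcome nor among the listed key secondary outcomes, and that the trial is a pilot that expects no significant difference.

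Four stronger readings might be inferred, and the document does not support them:

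- **No continuous outcome has a tDCS comparison.** The MRI and eye-tracking measures are continuous and do have a group comparison.
- **The post-quit period is ignored.** Abstinence is assessed over weeks 2 to 12 and analysed by chi-square and survival methods. Craving is also assessed before eye tracking at weeks 4, 8 and 12 and correlated with attentional bias. What is missing is an explicit ANOVA for the booster visits.
- **The trial's headline effect size is lost.** The protocol attaches partial eta-squared to consecutive days abstinent, which is not among the variables listed for this ANOVA. The loss shown here concerns the four listed measures.
- **The ANOVA will drop relapsers.** The protocol does not state complete-case handling, and missing-data rules may be in the statistical analysis plan. The ten sessions end at the target quit date, so absence from them cannot reflect relapse after quitting.

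**Conclusion.** The ANOVA is wrong as written. It contains a factor with one level and omits the only randomised factor. Of its 40 nominal parameters 20 can be estimated, and the arm contrast is outside the model. The promised active versus sham comparison, and a partial eta-squared for tDCS, cannot be obtained from it for craving, mood, cigarettes per day or CO. The same applies to the parallel follow-up ANOVAs if they keep these factors. The abstinence, MRI and eye-tracking analyses are untouched.

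The lack of an explicit ANOVA for the five booster visits is a fair secondary point. It rests on reading the ten levels as the ten daily sessions, which the count and the use of session 10 both support.

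The main conclusion needs no assumption about effect size, variance or missing data. The rank figures assume a full factorial model with both genders present in each arm.

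**What to change.** In Data Analysis:

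1. Replace Laterality with arm (active, sham), giving gender x arm x session.
2. Name the arm main effect and the arm x session interaction as the planned comparison, and report partial eta-squared for those terms.
3. State that the parallel follow-up ANOVAs carry the same arm factor.
4. State that the five booster visits (weeks 4, 6, 8, 10 and 12) are analysed with the same arm factor, either as a separate block or together with the daily sessions.

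A linear mixed model using all available visits is a reasonable option, but the correction does not depend on it. If session 1 is used as a covariate, take the score recorded on arrival: craving and withdrawal are recorded both on arrival and immediately after tDCS, and the later score may already carry a treatment effect.

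The cost is a wording change, best made before unblinding. It needs no new data, visits or participants, and SPSS and R, both named in the protocol, can fit either model.
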